## Abstract

**Background:**

Access to healthy food is considered a key determinant of dietary behavior, and there is mixed evidence that living near a supermarket is associated with a healthier diet. In Africa, supermarkets may contribute to the nutrition transition by offering both healthy and unhealthy foods and by replacing traditional food sellers. In Kisumu, Kenya, a planned hypermarket (ie, a supermarket combined with a department store) will form the basis for a natural experimental evaluation.

**Objective:**

The aim of this study is to explore the impacts of a new hypermarket on food shopping practices, dietary behaviors, physical activity patterns, and body composition among local residents and to identify concurrent changes in the local foodscape. We also aim to explore how impacts and associations vary by socioeconomic status.

**Methods:**

We employ a mixed methods, longitudinal study design. Two study areas were defined: the hypermarket intervention area (ie, Kisumu) and a comparison area with no hypermarket (ie, Homabay). The study is comprised of 4 pieces of primary data collection: a quantitative household survey with local residents, a qualitative study consisting of focus group discussions with local residents and semistructured interviews with government and private sector stakeholders, an audit of the local foodscape using on-the-ground data collection, and an intercept survey of shoppers in the hypermarket. Assessments will be undertaken at baseline and approximately 1 year after the hypermarket opens.

**Results:**

Baseline assessments were conducted from March 2019 to June 2019. From a total sampling frame of 400 households, we recruited 376 of these households, giving an overall response rate of 94.0%. The household survey was completed by 516 individuals within these households. Across the two study areas, 8 focus groups and 44 stakeholder interviews were conducted, and 1920 food outlets were geocoded.

**Conclusions:**

This study aims to further the understanding of the relationship between food retail and dietary behaviors in Kenya. Baseline assessments for the study have been completed.

**International Registered Report Identifier (IRRID):**

DERR1-10.2196/17814

## Introduction

Dietary behavior is complex and shaped by multiple interacting factors, including policy, built, and social environments [1]. Access to healthy food is considered a key determinant of dietary behavior, and some evidence suggests, albeit inconsistently, that residential proximity to a supermarket is associated with a healthier diet [2]. In high-income countries, there is mixed evidence that the establishment of a new supermarket influences health-related outcomes among local residents [3-5]. A review indicated inconsistent evidence that new supermarkets improve fruit and vegetable consumption and no evidence for changes in BMI or self-rated health [3]. However, further reviews of research from predominantly high-income countries suggested that interventions that involved manipulating the price or availability of products within grocery stores could increase the purchasing of healthier foods [6,7].

Evidence on the relationship between supermarkets, food purchasing, diet, and health is drawn mostly from high-income countries. There is an inadequate understanding of dietary behaviors and their drivers in low- and middle-income countries (LMICs). It is particularly important to understand dietary behaviors in these settings because of the ongoing nutrition transition that is typified by a movement away from traditional staples toward the consumption of cheap and highly processed food [8]. This is responsible, in part, for the emerging “triple burden of malnutrition,” whereby undernutrition and micronutrient deficiency coexist with obesity at population, household, and individual levels [9]. In Africa, the structure of the food retail market is changing rapidly as large supermarket chains expand into urban settings [10]. Supermarkets may play a key role in driving the nutrition transition through increasing the availability of processed food, though they may also sell healthy food cheaply or facilitate access to a wider range of foods [10,11]. Due to economies of scale, supermarkets are often able to sell items more cheaply than local traders and have been shown to displace smaller or informal local food outlets frequented by low–socioeconomic status (SES) households, generating or entrenching inequalities in food access and health [10].

Kenya is a low-income [12] East African country with a population of approximately 50 million [13]. Kenya is experiencing an escalating burden of noncommunicable disease and obesity [14,15], which is related, in part, to changing local diets. Kenya has a prospering supermarket sector [11], accounting for approximately 10% of the share of grocery sales at the national level, with a higher share in urban centers [16]. Evidence from Kenya suggests that living near, or shopping at, a supermarket increased the consumption of processed food at the expense of unprocessed food [11,16] and was associated with a higher BMI and metabolic syndrome in adults [16-18] but a lower probability of being underweight in children [17].

A new hypermarket (ie, a supermarket combined with a department store) is currently under construction at Lake Basin Mall in Kisumu, Western Kenya (see Figure 1). The mall, funded through a public-private partnership and currently planned to be the largest in Western Kenya, is located approximately 5 km from the central business district of the city of Kisumu, the seat of Kisumu County. The mall will house other amenities, such as an amphitheater, doctors’ offices, cafeterias, a gym, and office spaces. Lake Basin Mall is in close proximity to a higher-SES residential area but also close to lower-SES informal (ie, slum) settlements. It is situated along a busy highway that opens up the western part of Kenya, runs past Kisumu International Airport, and continues on toward Uganda’s Northern Transport Corridor, a popular destination for Kenyan traders in commodities such as fish, fruit, cereals, and animal feed.

**Figure 1 figure1:**
[figure not shown]
Images showing (a and b) the Lake Basin Mall site, (c) a scene from within the mall, and (d) the hypermarket site.

The opening of the hypermarket provides an opportunity to examine potential impacts on dietary behaviors among residents of Kisumu living nearby and on the local foodscape, using a natural experimental design [19], as well as the opportunity to explore whether impacts are distributed unequally or inequitably. Impacts will be examined relative to the town of Homabay in Homabay County, a neighboring comparison area where no hypermarket is planned. As such, the overall purpose of this study is to address the following research questions:

What are the individual, household, and population impacts of the new hypermarket at Lake Basin Mall on food shopping practices, dietary behaviors, physical activity patterns, and body composition among local residents across different SES groups?How has the local foodscape changed, do these changes relate to the new hypermarket at Lake Basin Mall, and how are they experienced by local residents?

## Methods

### Design

This is a protocol for a mixed methods, natural experimental study [20] that will use a combination of quantitative and qualitative research methods to evaluate changes in dietary and health behavior coupled with furthering an understanding of the drivers and impacts of these changes. As is typical for natural experimental studies, the intervention will not be under the control of researchers, and intervention assignment will not be randomized or blinded.

The study is comprised of four core pieces of primary data collection:

A longitudinal quantitative household survey with local residents.A longitudinal qualitative study consisting of focus group discussions with local residents and semistructured interviews with government and private sector stakeholders.A longitudinal audit of the local foodscape using on-the-ground data collection.A cross-sectional intercept survey of shoppers in the hypermarket.

The baseline data collection took place in 2019, before the anticipated opening of the hypermarket. The follow-up data collection is anticipated to take place in 2021, approximately 1 year after the hypermarket opens, which should provide sufficient time for shopping habits to adjust after an initial period where use of the hypermarket may be atypical. Assessments will ideally be seasonally matched (ie, they will take place at a similar time at both the intervention and comparison sites) to account for seasonal variation in behaviors. Should this not happen, seasonality will be addressed in the analysis. Modest incentives will be used to increase retention and to compensate for time spent participating in the study. The incentives include transport reimbursement, refreshments, and bars of soap as tokens of appreciation. If households subsequently move to outside the study areas, they will still be eligible for the follow-up assessment. Depending on attrition, we will also consider the possibility of recruiting a new sample of households from the study areas at follow-up.

### Setting

The study is set in Kisumu County and Homabay County in Western Kenya. Kisumu County has a population of 968,909, and Homabay County has a population of 963,794. Two study areas were defined: the hypermarket intervention area (ie, Mamboleo, Kisumu) and a comparison area with no hypermarket (ie, Sofia, Homabay). These areas were delineated using existing spatial census data, field visits, and local knowledge of the study investigators. A 2-km radial buffer was drawn around the hypermarket and matched according to population density with a 2-km radial buffer around another landmark in the comparison area. Therefore, both study areas are 2 km in size, by radius, and the two areas lie approximately 100 km apart.

Though we aimed to ensure similar aggregate socioeconomic characteristics and broadly similar topographical and food retail characteristics apart from the presence of a hypermarket, the sites are still somewhat heterogeneous. The intervention site may be considered urban and the comparison site maybe be considered periurban. However, both areas include a mix of lower- and higher-SES areas, both informal and formal settlements; both areas have a similar number of supermarkets and encompass the main shopping street; and both areas have major roads. Both areas are located on the shores of Lake Victoria, a freshwater lake and the traditional ancestral lands for the Luo ethnic community of Kenya; thus, they share similar cultural practices.

### Eligibility

#### Household Survey

Households living in one of the local study areas at baseline are eligible for the household survey. Individuals are considered household members if they regularly share meals, live together, and pool their monetary resources. A maximum of 5 adults, aged 18 years or over, in the household, including the head of household and the person who is usually responsible for food purchasing, will be eligible to complete interviewer-administered questionnaires and anthropometric measurements. The household head is the adult member of the household who is accepted and recognized by the other household members as the head, which implies a prominent role in making decisions that concern the household. Additionally, a maximum of 5 children, aged between 5 and 17 years, in the household will be eligible to complete anthropometric measurements. Households where either the head or the person responsible for food purchasing is under the age of 18 years will be excluded from the study.

#### Focus Groups

Adult householders from each of the local study areas who took part in the household survey will be eligible to participate in subsequent focus group discussions. These will be disaggregated into male and female as well as lower- and higher-SES groups. This was considered necessary to address any social, economic, cultural, or class issues that may impede free discussion. The focus group discussions will be conducted in local community halls owned by churches, local businesses, or the county government.

#### Stakeholder Interviews

Eligible stakeholders of interest include county government officers from the health, trade, agriculture, and infrastructure departments. Local administration representatives include the county commissioner and representatives of this office. Members of the Lake Basin Development Authority who developed the mall and hypermarket as well as representatives from the local food retail sector, such as the market master, are also considered important stakeholders. Other important local representatives include the motorcycle taxi (ie, boda boda) and fishing industries as well as local faith and religious leaders who are influential in the community.

#### Shopper Intercept Survey

Once the hypermarket is open, shoppers will be eligible to answer questions on their shopping habits and will be intercepted while they shop.

### Intervention

The intervention under study is the new hypermarket at Lake Basin Mall and its associated changes to the local foodscape. At the group level, the intervention dose is operationalized as the geographical proximity to the new mall (ie, living in either the intervention or comparison area). At the individual level, the intervention dose is operationalized according to whether the individual shops at the new hypermarket.

### Outcomes

The primary outcomes are as follows:

Change in the self-reported percentage share of monthly household food expenditure from supermarkets between baseline and follow-up.Changes in the number and type of local food outlets between baseline and follow-up.

The secondary outcomes are as follows:

Change in self-reported, monthly, household food expenditure, in Kenyan shillings, between baseline and follow-up.Change in self-reported household food security between baseline and follow-up.Change in self-reported individual dietary diversity (ie, number of food groups consumed on the previous day) between baseline and follow-up.Change in measured individual body composition (ie, BMI in kg/m^2^) between baseline and follow-up.Change in self-reported individual well-being between baseline and follow-up.An understanding of the changes that have occurred and how their effects have been experienced.

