#### Foodscape Audit

At baseline and follow-up, systematic on-the-ground data collection will be undertaken to geolocate and categorize food outlets in each of the local study areas. Teams of field workers will systematically walk around the study areas, coding the location and types of establishments and taking photos of food outlets. Data collection will be undertaken using electronic tablets. In addition, we will explore the availability and accuracy of existing data, such as county records of licensed food sellers.

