#### Foodscape Audit

Food outlets will be counted and categorized (eg, restaurant, kiosk, and supermarket) descriptively. Simple change scores will be calculated. Geospatial information will be imported into a GIS and used to inform analyses exploring distance between households and food outlets as well as density of food outlets.

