## Results

As of December 2020, we have undertaken initial stakeholder mapping and completed the baseline assessment. The follow-up assessment, data analysis, and publication are anticipated to take place in 2021.

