### Baseline Assessment

We undertook baseline assessments in Kisumu (ie, the hypermarket intervention area) in March 2019 and in Homabay (ie, the comparison area) in June 2019. From a total sampling frame of 400 households, we recruited 376 of these, giving an overall response rate of 94.0%. This exceeded our target of recruiting 250 households at baseline. Numbers of respondents completing each element of the assessment are reported in Table 1. We met or exceeded target sample sizes for all elements of the assessment.

**Table 1 table1:** Baseline assessment conducted in 2019.

Assessment		Kisumu (ie, hypermarket area), n (%)	Homabay (ie, comparison area), n (%)

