### Practical Challenges of Natural Experimental Designs

A defining feature of natural experimental designs is that the intervention of interest is not controlled by researchers, which can raise practical challenges for evaluation. Since the timing of the intervention is not under researcher control, it can be difficult to complete baseline assessments in the interval between the identification of the natural experiment opportunity and the implementation of the intervention. Equally, if an intervention is delayed, it can be difficult to complete an evaluation within the time constraints of research funding. In this study, the opening of the Lake Basin Mall and the hypermarket has been delayed. The baseline assessment has been completed, allowing detailed quantitative and qualitative exploration of associations between food retail, including supermarkets, and the outcomes of interest, which is an important contribution to the broader goal of understanding the role of food retail in shaping dietary and other health behaviors.

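### The outlet primary outcome is one change score from the 2019 baseline, and most of its window appears to precede the hypermarket's opening, with nothing planned to separate earlier from later change

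*Protocol article*

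**What the plan says.** The Outcomes section lists as a primary outcome "Changes in the number and type of local food outlets between baseline and follow-up". The Assessment section plans a walking audit at baseline and at follow-up, and none at opening. It adds that "we will explore the availability and accuracy of existing data, such as county records of licensed food sellers". Under Analysis Methods, outlets are counted and categorised descriptively, and "Simple change scores will be calculated". The second research question in the Introduction asks how the foodscape has changed and "do these changes relate to the new hypermarket at Lake Basin Mall".

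On timing, the Results section states: "We undertook baseline assessments in Kisumu (ie, the hypermarket intervention area) in March 2019 and in Homabay (ie, the comparison area) in June 2019". The Design section says: "The follow-up data collection is anticipated to take place in 2021, approximately 1 year after the hypermarket opens". The status line in Results reads: "As of December 2020, we have undertaken initial stakeholder mapping and completed the baseline assessment". The Introduction describes the store as still being built, and the Discussion says: "In this study, the opening of the Lake Basin Mall and the hypermarket has been delayed".

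**The concern.** A change score between two audits gives the same +1 to an outlet that began trading in mid-2019 and to one that began after the hypermarket opened. Closures are treated alike in the same way. That matters little when the intervention follows soon after baseline. Here the opening slipped, and the outcome definition and analysis were not adapted to the delay.

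At stake is the answer to the second research question. If outlet turnover before opening differed between Kisumu and Homabay, that difference sits inside the contrast from which any link to the hypermarket would be argued. It could go either way: unrelated growth in Kisumu could hide displacement of small sellers, and unrelated decline could imitate it.

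**Working it through.** **Plan's own figure.** There is none to reproduce for this outcome. The sample size section covers only the expenditure-share outcome.

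**Inputs.** Baseline is March 2019 (Kisumu) and June 2019 (Homabay), from Results. Follow-up is about 12 months after opening, from Design. The opening date is not given. December 2020 is taken as the earliest date consistent with the status line, the description of the store as unfinished and the reported delay. I assume that both areas are followed up in the same month.

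**Formula.** Pre-opening months = opening month minus baseline month. Window = pre-opening months + 12. Share = pre-opening months / window.

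| Assumed opening | Kisumu | Homabay |
|---|---|---|
| January 2020 (early case under a 2021 follow-up) | 10/22 = 45% | 7/19 = 37% |
| December 2020 (earliest fitting the status) | 21/33 = 64% | 18/30 = 60% |
| June 2021 | 27/39 = 69% | 24/36 = 67% |

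The first row only shows what the timetable alone would allow; the December 2020 status overtakes it. If follow-up were held in 2021 despite a later opening, the share would rise further. With opening in January 2021 and follow-up in June 2021 (both assumed), it is 22/27 = 81% in Kisumu.

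**What a differential trend could do.** The baseline counts are 1008 outlets in Kisumu and 912 in Homabay. No growth rate is given, so the rates below are assumptions that show only the range. Spurious Kisumu excess after one pre-opening year = 1008 × g(Kisumu) − 912 × g(Homabay):

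- 5% and 2%: 50.4 − 18.2 = +32 outlets
- 3% in both: 30.2 − 27.4 = +3 outlets
- 2% and 5%: 20.2 − 45.6 = −25 outlets

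The sign follows from the assumption, so this is no estimate of bias.

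**Check on an obvious remedy.** Dating new outlets invites a comparison of opening rates before and after within Kisumu. That comparison is biased. An outlet that opened and closed between the audits is seen by neither, and earlier openings have had longer to disappear. Take a constant opening rate and a constant closure hazard h per year, with one year on each side of opening. Survivors from the later year relate to survivors from the earlier year as ∫₀¹e^(−hs)ds to ∫₁²e^(−hs)ds, a ratio of e^h. For an assumed h of 0.1 the ratio is 1.11, and for 0.3 it is 1.35. The later period would seem to have 11% to 35% more openings with no true change.

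**The case against.** A baseline before opening is required in a two-wave natural experiment, the investigators do not control the opening date, and the Discussion reports the delay openly. Nothing in the plan is contradictory here. The Introduction says that impacts are examined relative to Homabay, which is audited over nearly the same interval, so shared turnover cancels. Stakeholder interviews, focus groups, distance and density analyses and the mixed methods step also bear on attribution. The Discussion names unmeasured confounding from concurrent changes as a core limitation. All of this stands, and it limits the point to differential pre-opening turnover.

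A reader might infer several stronger things that the documents do not support:

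- **That the raw Kisumu change will be read as impact.** No section says so. The audit analysis is described as descriptive, and the stated frame is comparative, although the audit analysis paragraph does not itself name the between-area contrast.
- **That Homabay is of no use because supermarket chains expand into cities.** That background remark concerns large chains, not turnover among 1920 outlets of all types, and the Setting section says that the areas have similar numbers of supermarkets.
- **That the audit holds no dates at all.** The article condenses the audit, the form is not shown, and licence records are to be explored. What can be said is that the stated outcome and analysis use no dates.
- **That all pre-opening change is noise.** The Intervention section includes associated foodscape changes, so outlets that opened or left in anticipation of the mall may belong to the effect.

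**Conclusion.** The point holds as a limitation that can be reduced at low cost. On the article's own dates, at least about 64% of the Kisumu window and 60% of the Homabay window precede opening. This rests on two conditions: that the store was unopened in December 2020, which is inferred, and that follow-up is 12 months after opening. The planned change score cannot separate that period from the post-opening year. The Homabay contrast removes common turnover but not turnover that differs between an urban and a periurban site. With one area per arm and two audits, equality of pre-opening trends cannot be checked. The size and direction of any resulting bias cannot be derived from the documents.

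**What to change.** 1. At the follow-up audit, record the month and year in which each outlet absent from the baseline file began trading at its site.
2. In the foodscape analysis, keep the planned change score and state it as a Kisumu–Homabay contrast.
3. Beside it, report surviving new outlets in both areas as opened before or after the hypermarket's opening date. Base the statement on whether new outlets relate to the hypermarket mainly on the between-area contrast in post-opening openings.
4. Show pre-opening openings separately, as background or possibly anticipatory change.
5. Do not compare before and after rates within an area, because unseen short-lived outlets lower the earlier count more.
6. Date closures only where county licence records allow, and report the rest as undated.

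The cost is one short question at new outlets in a follow-up that had not yet taken place at the December 2020 status, plus a date split in the analysis. Start dates will carry recall error and closure dates will be incomplete. The post-opening contrast still misses outlets that came and went within the year, which biases it only so far as closure rates differ between the areas. No data already collected are lost.

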### Assessment

#### Household Survey

At baseline and follow-up, participants will complete a household and an individual questionnaire. The household questionnaire will be completed by the head of household and by the person who is usually responsible for food purchasing and will assess the following variables:

Demographic variables for each individual in the household (ie, age, sex, relationship to head of household [eg, wife or child], ethnicity, education, and occupation).Characteristics of the household (ie, housing tenure and quality, access to electricity and water, appliance used for cooking, refrigerator ownership, car ownership, and duration of residence in the area).Household food purchasing in the previous month, including sources of food, types of food retail accessed, and amount of money spent at different types of food retailers and overall.Number of trips made to purchase food and modes of transport used in the previous month.Household food security, based on the Food and Agriculture Organization’s Food Insecurity Experience Scale [24].

The individual questionnaire will be completed by each eligible adult, aged 18 years or over, and will assess the following variables:

Dietary diversity using an unquantified 24-hour dietary recall and following the approach described by the Food and Agriculture Organization and the United States Agency for International Development’s Food and Nutrition Technical Assistance III Project [25]. In order to calculate a dietary diversity score, the range of foods and drinks consumed will be classified into 10 core food groups: grains, white roots, tubers, and plantains; pulses; nuts and seeds; dairy; meat, poultry, and fish; eggs; dark green leafy vegetables; other vitamin A–rich fruit and vegetables; other vegetables; and other fruit.Physical activity, using the World Health Organization Global Physical Activity Questionnaire [26].Well-being, using two items from the abbreviated version of the World Health Organization Quality of Life instrument [27].Social connectedness, using 3 items from the Social Provisions Scale [28].

Following this, all eligible participants in the household, both adults and children, will complete anthropometric measurements (ie, height, weight, and waist circumference) using standard procedures. A tape measure, stadiometer, and calibrated scales will be used. Each measurement will be taken in duplicate.

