### Analysis Methods

#### Household Survey

For all quantitative analyses, the level of statistical significance will be set as α<.05. All participants who provide data will be included in analyses, and we will not impute missing data. Net changes between baseline and follow-up will be computed, and significance tests will be conducted using a method appropriate to the distribution of the data. Differences in means will be compared using *t* tests or analyses of variance for normally distributed variables, while medians will be compared using the Wilcoxon rank-sum test or the Kruskal-Wallis test for skewed data. We will further undertake multivariable regression analyses adjusted for important covariates, using models appropriate to the distribution of the data and accounting for clustering by household. For binary outcomes, we will explore the use of logistic regression models, and for continuous outcomes we will consider linear regression models and negative binomial or zero-inflated generalized linear models. Regression estimates and 95% confidence intervals will be reported.

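### The only body-composition metric stated is change in raw BMI (kg/m²), yet children aged 5–17 are measured too; growth enters their change scores unless adults and children are separated

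*Protocol article*

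**What the plan says.** Protocol article, Outcomes: the list of secondary outcomes has "Change in measured individual body composition" and equates it, by an ie, with BMI in kg/m², taken from baseline to follow-up. The abbreviation and the unit fix raw BMI as the metric.

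Eligibility, Household Survey: besides up to five adults, "a maximum of 5 children, aged between 5 and 17 years, in the household will be eligible to complete anthropometric measurements". Assessment, Household Survey: "all eligible participants in the household, both adults and children, will complete anthropometric measurements". The individual questionnaire, by contrast, is for adults only, so among the listed individual-level outcomes BMI is the only one that the children's measurements can feed.

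Analysis Methods, Household Survey: the inclusion rule is "All participants who provide data will be included in analyses, and we will not impute missing data". On change scores the section says "Net changes between baseline and follow-up will be computed", with testing by t tests, analysis of variance or rank tests. These are followed by "multivariable regression analyses adjusted for important covariates", with the covariates not named.

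Introduction: earlier Kenyan evidence on living near or shopping at a supermarket is summarised as "associated with a higher BMI and metabolic syndrome in adults [16-18] but a lower probability of being underweight in children [17]".

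**The concern.** A child's BMI changes with age, at a rate that depends on age and sex, whether or not a hypermarket opens. Raw change in kg/m² is a reasonable measure for adults but not for people who are still growing. If both are analysed as one set of change scores, two problems follow.

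- **Growth is mixed with effect.** Each child's change contains growth in full. The mean change within an area is shifted, and its variance rises because children and adults have different expected changes. Any imbalance between the areas in who is measured, or for how long, then looks like an effect of the hypermarket.
- **The pooled mean is hard to interpret.** On the article's own background, a rise in BMI may be unwelcome in adults and, where it reflects less underweight, welcome in children. One average over both does not say which has happened.

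**Working it through.** The article gives no effect size, standard deviation or sample size for BMI. Its only sizing calculation concerns expenditure share, so there is no plan figure to reproduce here.

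**Inputs from the article**
- Baseline: March 2019 in Kisumu, June 2019 in Homabay (Baseline Assessment).
- Follow-up: anticipated in 2021, about one year after opening (Design); the opening has been delayed (Practical Challenges of Natural Experimental Designs).
- Sites: not fully alike, the intervention site being urban and the comparison site periurban (Setting).
- Child share: not given. Table 1 reports 516 individuals without an age breakdown.

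**Assumptions**
- Growth g = 0.3–0.8 kg/m² per year in children.
- Child share p = 20–60% of those measured.
- Interval T = 2 years for the illustrations.

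**Step 1: interval.** With follow-up between January and December 2021:
- Kisumu: 22 to 33 months.
- Homabay: 19 to 30 months.

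The delay makes the later end more likely.

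**Step 2: drift within one area from growth alone**, g × p × T:
- Low: 0.3 × 0.20 × 2 = 0.12 kg/m².
- High: 0.8 × 0.60 × 2 = 0.96 kg/m².

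**Step 3: what is left in the between-area contrast.** If child share, age mix and interval are equal in both areas, growth cancels. If they are not:
- Child share differs by 10 points, g × T × 0.10: from 0.3 × 2 × 0.10 = 0.06 to 0.8 × 2 × 0.10 = 0.16 kg/m².
- Interval differs by 3 months, g × p × 0.25: from 0.3 × 0.20 × 0.25 = 0.015 to 0.8 × 0.60 × 0.25 = 0.12 kg/m².

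The 3-month case is realistic. Baselines were 3 months apart, and the Design section's idea of seasonal matching is to assess both sites at a similar time. If that is achieved at follow-up, Kisumu's interval will be about 3 months longer. If the follow-ups are staggered as the baselines were, this term disappears.

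**Step 4: participants who change age group.** Everyone aged 17 at baseline will be 18 or over at follow-up. At the shortest interval (19 months) a child who had just turned 16 would still be 17; at 24 months or more, all 16-year-olds will have become adults. A rule is needed for those who cross.

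**The case against.** The strongest reply is that the article never says adults and children will be pooled. In the outcome list, the term individual also describes dietary diversity and well-being, which come from an adults-only questionnaire, so it may simply mean not household-level. Measuring children is not the same as averaging them with adults. A condensed article may also leave covariates and subgroup handling to a fuller document, and age and sex are recorded for every household member. This stands in part: pooling is an inference from the eligibility, assessment and analysis sections together. It does not dispose of the point. The article is not silent on the metric; it names one, and that is the only metric stated for the children it measures. Adjustment for unnamed covariates is not a sure remedy either, since a single age term across adults and children would not describe growth confined to the young.

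Several stronger readings are tempting but not supported:
- *Growth is simply counted as a hypermarket effect.* Impacts are to be judged against the comparison area, so growth common to both areas cancels.
- *The interval is at least two years.* The dates allow 19–33 months.
- *The error among children could reach 0.6 kg/m².* One gets this by assuming growth of 0.4 kg/m² per year in one area and 0.7 in the other for two years, 2 × (0.7 − 0.4). Nothing in the article places the two areas at opposite ends of such a range.
- *Effects in adults and children are expected to run in opposite directions.* Higher adult BMI and less childhood underweight both point upward; they differ in health meaning, not in sign.
- *All 16- and 17-year-olds will be adults at follow-up.* This is certain only for the 17-year-olds.

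**Conclusion.** The point holds in a limited form. The article fixes a metric that does not suit part of the population it measures, and nothing in it separates that part out. Within-area change and its variance would carry children's growth in full. The between-area contrast is exposed only through differences in child share, age mix or interval. Under the stated assumptions, the residual is about 0.06–0.16 kg/m² for a 10-point difference in child share and 0.015–0.12 kg/m² for a 3-month difference in interval. No imbalance in child share or age has been shown, because the article gives no ages by area; the difference in baseline dates is documented. BMI is a secondary outcome, and neither the primary outcomes nor the sample size is touched. The change should be made because it is cheap and because a pooled mean would be hard to interpret even with well-balanced areas.

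**What to change.** Divide the outcome in the Outcomes section, and mirror the division in Analysis Methods:

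- *Adults (18 or over at baseline): change in BMI in kg/m² between baseline and follow-up.*
- *Children (5–17 at baseline): change in age- and sex-standardised BMI-for-age z-score between baseline and follow-up, analysed separately and not pooled with adults.*

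Fix group membership by age at baseline. Name the growth reference, and state what happens to participants who pass its upper age by follow-up, for example exclusion from the child z-score analysis.

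The cost is a wording change and one small additional analysis. Age, sex, height and weight are already collected, and the Results section reports that, as of December 2020, follow-up and analysis were still to come. The kg/m² analysis would rest on fewer people than a pooled one, and excluding those who outgrow the reference would lose some of the oldest children.
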